# Acupuncture for the treatment of phantom limb pain in lower limb amputees: study protocol for a randomized controlled feasibility trial

**DOI:** 10.1186/s13063-015-0668-3

**Published:** 2015-04-12

**Keywords:** Acupuncture, feasibility studies, pain, phantom limb

## Abstract

**Background:**

Phantom limb pain is a prevalent condition that is difficult to manage, with a lack of robust evidence to support the use of many adjunctive treatments. Acupuncture can be effective in the management of many painful conditions but little is known about its effectiveness in treating phantom limb pain. The aim of this study is to explore the feasibility of conducting a randomized controlled trial comparing acupuncture and routine care in a group of lower limb amputees with phantom limb pain.

**Methods/design:**

An unstratified, pragmatic, randomized, two-armed, controlled trial of parallel design comparing acupuncture and usual care control will be conducted. A total of 20 participants will be randomly assigned to receive either usual care or usual care plus acupuncture. Acupuncture will include eight 1 hour treatments delivered pragmatically over 4 weeks by practitioners trained in traditional Chinese medicine. As outcome measures, the Numerical Pain Rating Scale, short-form McGill Pain Questionnaire 2, EQ-5D-5 L, Hospital Anxiety and Depression Scale, 10-Item Perceived Stress Scale, Insomnia Severity Index, and Patient Global Impression of Change will be completed at baseline, weekly for the duration of the study and at 1 month after completion of the study. After completion of the trial, participants will provide feedback though semi-structured interviews.

Feasibility will be determined through the ability to recruit to the study, success of the randomization process, completion of acupuncture intervention, acceptability of random allocation and completion of outcome measures. Acceptability of the acupuncture intervention will be determined through semi-structured interviews with participants. The appropriateness of outcome measures for a future trial will be addressed through completion rates of questionnaires and participant feedback.

**Discussion:**

Data generated on effect size will be used for future sample size calculations and will inform the development of an appropriate and feasible protocol for use in a definitive multicentre randomized controlled trial.

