The objectives of this study are to: (1) explore the feasibility of recruiting, randomizing and retaining participants; (2) evaluate the feasibility and acceptability of including a standard care control; (3) evaluate the adherence or compliance and acceptability of acupuncture as an intervention; (4) evaluate the appropriateness of outcome measures and their completion rates and explore participants’ experience in completing outcome measures; (5) identify appropriate primary and secondary outcome measures that could be used in future trials; (6) explore the perceived effectiveness of acupuncture in treating phantom limb syndrome; (7) generate data on effect size for use in future sample size calculations; and (8) inform the development of an appropriate and feasible protocol for use in a definitive multicentre randomized controlled trial.

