### Recruitment

Participants will be approached and recruited whilst they are inpatients at the Amputee Rehabilitation Unit. Newly admitted potential participants will be identified by clinical staff (JG, CC), approached by the researcher ([name]), initially screened, and provided with oral and written information. Participants who pass initial screening tests and are willing to participate will have a final eligibility check by [name] before enrolment in the study (Figure 1). Signed, informed consent will be obtained from all participants before enrolling them in the study. Those declining to participate will be asked briefly for their reasons. As the study is a feasibility study, no sample size calculation has been performed [21]. An arbitrary number of 20 participants was deemed adequate to provide information on recruitment, randomization and acceptability of acupuncture and answer the objectives of this trial [23].

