### Randomization, allocation concealment and blinding

Randomization and allocation concealment will be used to ensure against selection bias [29]. Prior to commencement of the study, a researcher (NR) not involved in the day-to-day execution of the study will randomly allocate and conceal allocation. A copy of the randomized sequence will be kept in a locked cabinet and not shared with study personnel. The researcher ([name]) who will enrol participants and assign them to either acupuncture intervention or control will not know the random sequence or treatment allocation.

Randomization will be achieved using a computer-generated random numbers table and will be unstratified and balanced (1:1). Permuted blocking will be used to achieve balance between study arms. A block size of four will be used in this study. Allocation concealment will be implemented using sequentially numbered, opaque sealed envelopes. The envelopes will be opened sequentially only after participant’s details are written on each envelope.

Participants and practitioners involved in the study will not be blinded. However, the researcher collecting outcome measures ([name]) will be blind to the participant’s allocation.

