### Analysis

As this is a feasibility study, emphasis will be on feasibility and not on statistical significance of results [21]. Compliance with the protocol will be examined through number counts on drop outs or numbers of missed treatments, completion rates of outcome measures, and their perceived appropriateness and deviation from the protocol. Data will be collected on the use of rescue medication and adverse events (captured through open-ended prompts by practitioners at each intervention time point). Details of any participants who are excluded from the study will be reported and exclusion will be distinguished from attrition.

All statistical analysis will be undertaken using SPSS Version 21 software. The analysis will test for within-patient and between-group differences in measurements taken at the beginning of the study, during the study, at the end of the study and one month after completion of the study. An intention-to-treat approach will be taken [44]. To include missing data, any missing data will be imputed using the last observation carried forward [45].

The null hypothesis is that there is no difference in change in the primary outcome measure between group A and C at the end of intervention (end of week 4). Statistical analysis will be performed to verify rejection of the null hypothesis with a *P* = 0.05 taken as indicative of statistical significance. Nonparametric tests will be used in inferential analysis. The nonparametric Mann–Whitney *U* test will be used for analysis between groups. The difference between baseline and last observation scores will be analyzed using Wilcoxon signed-rank test. The effect size (Cohen’s *d*) will be calculated to provide information on the relative magnitude of difference [46]. All secondary outcome measures will be treated in the same way as the primary outcome. Categorical and continuous baseline characteristics will also be analyzed to test for between-group differences.

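### Cohen's d from 10 participants per arm is too imprecise to set the definitive trial's target difference, yet the protocol sends effect-size data into its sample size calculation

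*Protocol article*

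**What the plan says.** The Discussion part of the Abstract states "Data generated on effect size will be used for future sample size calculations". Objective 7, at the end of the Background, is to "generate data on effect size for use in future sample size calculations". The Analysis section is the only place where the effect size is given a form. It is Cohen's d, which "will be calculated to provide information on the relative magnitude of difference".

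On size, the Abstract says "A total of 20 participants will be randomly assigned to receive either usual care or usual care plus acupuncture". The Recruitment section says "As the study is a feasibility study, no sample size calculation has been performed" and then "An arbitrary number of 20 participants was deemed adequate to provide information on recruitment, randomization and acceptability of acupuncture". The same sentence extends that adequacy to the trial's objectives, and objective 7 is one of them.

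The main Discussion adds a caution: inferential tests serve only to pilot the procedure and are not to be read as evidence of effectiveness. It says nothing comparable about using the effect size for planning.

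**The concern.** The number 20 is defended for recruitment, randomization and acceptability, and for those purposes it may serve. Estimating a treatment effect is a different task. With 10 per arm, the sampling error of d is as large as most effects a pain trial could hope to find. If that estimate sets the target difference, chance largely decides the size of the definitive trial.

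The two directions of error do not have the same consequences. A d at or below zero gives no usable superiority sample size. The pilots most likely to lead to a calculation are those with a positive estimate, and these overstate the effect on average. The risk is a definitive multicentre trial that is too small, in a population where this protocol's own success criterion is only two recruits a month.

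**Working it through.** **Inputs from the protocol.** 20 participants allocated 1:1 in blocks of four give five full blocks, so 10 per arm and 18 degrees of freedom. Alpha is 0.05. Last observation carried forward keeps the nominal number at 10 per arm. At the 90% completion target, about 9 per arm would actually be observed, which makes matters slightly worse.

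**Assumptions, because the protocol gives no figure.** Two-sided test; 80% power for the definitive trial; normal outcomes; true d between 0.2 and 1.0. There is no sample size calculation in the protocol to reproduce.

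**1. Precision of d.** With t = d × √(n/2) = d × √5, the 95% interval comes from inverting the noncentral t distribution on 18 degrees of freedom.

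| Observed d | 95% CI |
|---|---|
| 0.2 | -0.68 to 1.08 |
| 0.3 | -0.59 to 1.18 |
| 0.5 | -0.40 to 1.38 |
| 0.8 | -0.12 to 1.70 |
| 1.0 | 0.05 to 1.92 |

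Check at d = 0.5: SE = √(2/10 + 0.25/40) = 0.454, so the half-width is about 0.89. The interval excludes zero once d × √5 exceeds 2.101, that is, once d exceeds 2.101/2.236 = 0.94.

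**2. What this means for a sample size.** The normal formula is n per arm = 2(1.960 + 0.842)²/d² = 15.70/d².
- d = 0.5: 62.8, so 63 (64 with the t distribution).
- d = 1.38, the upper limit: 8.2, so 9 (10 with the t distribution).
- d = -0.40, the lower limit: no superiority trial can be sized.

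**3. Realised power if the definitive trial is sized on the observed d.** The trial falls short of 80% power when the observed d exceeds the true d, apart from the effect of rounding n up. So P(under 80% | observed d > 0) ≈ P(observed d > true d) / P(observed d > 0).
- True d 0.2: 0.502/0.673 = 75%.
- True d 0.5: 0.506/0.868 = 58%.
- True d 0.8: 0.510/0.963 = 53%.

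Simulation with 1,000,000 pilots per scenario, rounding n up:

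| True d | Under 80% power, all pilots | Under 80% power, observed d > 0 | Mean power, observed d > 0 |
|---|---|---|---|
| 0.2 | 50% | 75% | 44% |
| 0.3 | 50% | 67% | 54% |
| 0.5 | 50% | 58% | 65% |
| 0.8 | 50% | 52% | 73% |
| 1.0 | 49% | 50% | 75% |

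At true d 0.5, power is below 50% in 37% of the pilots with a positive estimate.

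**4. What 10 per arm can supply.** The SD has 95% limits of √(18/31.53) = 0.76 and √(18/8.23) = 1.48 times its estimate. Suppose the target difference is fixed externally and equals the true difference. Power is then about Φ(2.80 × s/σ - 1.96), where s is the pilot SD and σ the true SD. With the SD taken as estimated, power is below 80% in 54% of cases, but the shortfall is mild: mean power is 77%, and power is below 50% in only 4%. The one-sided 80% upper limit multiplies the SD by √(18/12.86) = 1.18 and n by 18/12.86 = 1.40. By construction it cuts the chance of an SD that is too small to 20%.

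**The case against.** The strongest reply is that the text promises less than one may read into it. It says effect-size data will be used; it does not say that the point estimate will be the only input. The Analysis section gives the purpose of d as describing magnitude, and the link to sizing comes from reading it together with the Abstract and objective 7. An interval for d may well be specified in a fuller document that is not shown. The definitive trial will also have its own protocol and its own justification. All of this stands, and it limits the point to how the pilot d may be used. It does not remove the point, because these passages commit effect-size data to planning, define no other effect size, and call 20 sufficient for the objectives.

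Some stronger readings are tempting and are not supported.
- A reader might infer that the definitive trial will more likely than not be underpowered. A wide interval alone does not give that: over all pilot results the chance is about 50%. It exceeds half only once a positive estimate is required, and the success criteria in the Analysis section contain no threshold on d or P. By a true d of 1.0 it is back to 50%.
- A reader might infer that the interval must run from harm to a very large benefit. That depends on a result not yet seen, and it fails from an observed d of about 0.94 upward.
- A reader might infer that objective 7 cannot be met. The objective is to generate data, and the trial will do so, imprecisely.

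The Analysis section also says "Statistical analysis will be performed to verify rejection of the null hypothesis", at the 0.05 level. The stated emphasis on feasibility and the caution in the main Discussion deal with that adequately. The pairing of d with rank tests and the roughly 4% small-sample bias of d are trivial beside a half-width of about 0.9.

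**Conclusion.** The point holds in a limited form. The protocol treats an arbitrary 10 per arm as sufficient for an objective that feeds effect-size data into a sample size calculation. A d of that precision should not set the target difference, and the caution in the main Discussion covers hypothesis tests, not sizing.

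The size of the problem is an interval of about ±0.9 around d. If sizing follows a positive estimate, the probability of under 80% power is about 75%, 58% and 52-53% at true d 0.2, 0.5 and 0.8. These probabilities rest on the assumptions listed with the working and on the condition of a positive pilot estimate. The imprecision of d follows from 10 per arm under normal outcomes alone. The consequence falls on the next trial; the conduct and feasibility criteria of this one are unaffected.

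**What to change.** In the Discussion part of the Abstract, objective 7 and the Analysis section, state that the pilot d will not set the definitive trial's target difference. Suggested wording for objective 7: estimate the variability of the pain rating and its correlation between baseline and week 4, to inform future sample size calculations.

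In the Analysis section, report the between-group mean difference in the numerical rating scale at week 4, in points, with a 95% confidence interval, the pooled SD and the baseline to week-4 correlation. If d is shown, give its confidence interval.

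Base the definitive trial on a minimum clinically important difference on the rating scale, justified from outside this trial. Use an upper confidence limit for the SD, for example the one-sided 80% limit (1.18 times the estimate, so n × 1.40).

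The cost is wording and a few statistics from data already to be collected. The downside is that the next trial's planned size becomes somewhat larger.

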**Trial registration:**

ClinicalTrials.gov: NCT02126436.

**Electronic supplementary material:**

The online version of this article (doi:10.1186/s13063-015-0668-3) contains supplementary material, which is available to authorized users.

## Background

Phantom limb pain, defined as painful sensations perceived in the missing portion of the amputated limb [1], was recorded medically as early as the sixteenth century by Ambroise Paré [2]. It is very common and prevalence may be as high as 75 to 80% [3,4].

Treatment of phantom limb pain includes such interventions as pre-emptive analgesia, pharmacological interventions, neuromodulation and supportive nonpharmacological or noninvasive techniques, such as mirror therapy, graded motor imagery and stump liners. Evidence suggests that pre-emptive epidural and perineural analgesia might not prevent chronic phantom limb pain [5,6]. Pre-emptive gabapentin has also been found to be ineffective [7]. Pharmacological interventions, including morphine, gabapentin and ketamine, may provide short term analgesic efficacy [8]. There is a lack of robust evidence to support the use of neuromodulation [9], mirror therapy [10] or graded motor imagery [11]. One randomized controlled trial suggested that stump liners might reduce phantom limb pain [12] but the sample size in this study was small.

Acupuncture has been shown to be an effective intervention in the management of many pain conditions [13-15] but little is known about the effectiveness of acupuncture for the treatment of neuropathic pain [16]. Specifically, the effectiveness of acupuncture for treating phantom limb pain has not been widely assessed or documented, with most of the literature consisting of case reports [17,18]. Although these studies generally report positive outcomes [17], they are at the bottom of the hierarchy of evidence [19]. A systematic review including English, Chinese and Korean databases identified only two nonrandomized controlled trials evaluating the effectiveness of acupuncture. Although these studies reported positive outcomes, both were deemed to have a high risk of bias and low methodological quality [20]. Further research is needed to evaluate the effectiveness of acupuncture for treating phantom limb pain but, prior to a definitive trial, a study is needed to determine feasibility [21].

The objectives of this study are to: (1) explore the feasibility of recruiting, randomizing and retaining participants; (2) evaluate the feasibility and acceptability of including a standard care control; (3) evaluate the adherence or compliance and acceptability of acupuncture as an intervention; (4) evaluate the appropriateness of outcome measures and their completion rates and explore participants’ experience in completing outcome measures; (5) identify appropriate primary and secondary outcome measures that could be used in future trials; (6) explore the perceived effectiveness of acupuncture in treating phantom limb syndrome; (7) generate data on effect size for use in future sample size calculations; and (8) inform the development of an appropriate and feasible protocol for use in a definitive multicentre randomized controlled trial.

## Methods/design

### Design

A comparative effectiveness feasibility study will be conducted, using a mixed-methods approach, including a small randomized controlled trial and semi-structured interviews. The randomized controlled trial will be an unstratified, open, pragmatic, effectiveness trial, of parallel design, with two arms, using balanced randomization between acupuncture and usual care and a usual care control. Cross-sectional interviews will be carried out at the end of the intervention period.

Ethical approval was granted from the National Research Ethics Service Committee London (Bloomsbury) in July 2014 and Guy’s and St Thomas’ R & D and London South Bank University in October 2014. The trial is registered with ClinicalTrials.gov (NCT02126436) https://www.clinicaltrials.gov/ct2/show/study/NCT02126436 and will be conducted in compliance with the principles of the Declaration of Helsinki [22] the London South Bank University Code of Practice, and the London (Bloomsbury) Research Ethics Committee.

### Study settings

The study will be conducted at the Amputee Rehabilitation Unit, at Lambeth Community Care Centre, London, Guy’s and St Thomas’ NHS Foundation Trust. The Amputee Rehabilitation Unit is a 12-bed inpatient unit that provides specialist rehabilitation after major amputation. It accepts both primary and established amputees who have undergone a functional decline for approximately 7 weeks of evidence-based care, including access to specialist medical, nursing, therapy, and counselling professionals. Acupuncture will be provided at the Gateway Acupuncture Clinic (which is located in the same building) and provides an NHS acupuncture service through GP referral, in the area of Lambeth and Southwark. The clinic provides treatment for chronic long-term conditions, specializing in chronic pain, headaches, migraines and HIV.

### Recruitment

Participants will be approached and recruited whilst they are inpatients at the Amputee Rehabilitation Unit. Newly admitted potential participants will be identified by clinical staff (JG, CC), approached by the researcher ([name]), initially screened, and provided with oral and written information. Participants who pass initial screening tests and are willing to participate will have a final eligibility check by [name] before enrolment in the study (Figure 1). Signed, informed consent will be obtained from all participants before enrolling them in the study. Those declining to participate will be asked briefly for their reasons. As the study is a feasibility study, no sample size calculation has been performed [21]. An arbitrary number of 20 participants was deemed adequate to provide information on recruitment, randomization and acceptability of acupuncture and answer the objectives of this trial [23].

**Figure 1 Fig1:**
[figure not shown]
Participants’ flow through the study. The different phases of the study and participants’ flow through the study with details on timings of the different phases of the study. ARU, Amputee Rehabilitation Unit; GP, general practitioner; HADS, Hospital Anxiety and Depression Scale; ISI, Insomnia Severity Index; NPS, numerical pain scale; PGIC, Patient Global Impression of Change; PSS-10, 10-Item Perceived Stress Scale; SF-MPQ-2, short-form McGill Pain Questionnaire 2.

### Eligibility criteria

Participants will be included if they: (1) at least 18 years of age, (2) have full cognitive ability and are able to communicate in English, (3) have traumatic or medical amputation of a lower limb (greater than toes), and (4) are currently experiencing phantom limb pain of ≥5 on an 11-point verbal rating scale (that is, moderate or severe phantom limb pain) [24]. Participants will be excluded if they: (1) have congenital limb absence, (2) are medically too unwell (as advised by medical staff at the Amputee Rehabilitation Unit), (3) are pregnant, or (4) where acupuncture is cautioned, including participants with poorly controlled epilepsy, severe haemophilia or other bleeding or clotting disorders, or a pacemaker (if using electro-acupuncture), and patients undergoing or who have recently undergone chemotherapy or bone marrow transplant, any skin changes or removal of lymph nodes in the body, that would preclude placement of acupuncture needles [25].

### Intervention (RCT)

The acupuncture group (group A) will receive usual inpatient care and a course of acupuncture. The control group (group C) will receive usual inpatient care only. Usual care will include both medical intervention and daily physiotherapy and rehabilitation, as routinely provided at the Amputee Rehabilitation Unit.

All acupuncture practitioners involved in the study will be trained in the practice of traditional Chinese medicine. All practitioners will be members of the British Acupuncture Council, will have at least 15 years clinical experience and will follow the safety guidelines of the British Acupuncture Guide to Safe Practice [25]. Acupuncture needles will be single-use, presterilized, disposable, solid, stainless steel needles (with prepacked single-use guide tubes if guide tubes are used). The acupuncture intervention will be pragmatic but will be guided by a protocol previously developed though a Delphi practitioner consensus study [26]. This protocol advises:Using a combination of body and auricular acupuncture;Treating the contralateral limb and possibly the ipsilateral limb;Including auricular acupuncture points such as shen men, sympathetic and points corresponding to the lower limb;Depending on the health of the tissue and the individual participant, needling around the stump;Mirroring local and distal points by needling the opposite limb;Including points on the lower back (taking a segmental approach to dermatomal pain);Including points such as LI4 + LR3, LR3, GV20, SP10 and also specified points according to participants’ specific symptoms;Retaining needles for 20 to 30 minutes.

No set criteria will be followed when needling, other than to follow the guidelines of the protocol. Practitioners will assess and treat participants under the paradigm of traditional Chinese medicine. Treatment may (depending on the practitioner’s diagnosis and treatment plan) include electro-acupuncture or other adjunctive interventions, such as cupping. All participants in group A will receive eight one-hour acupuncture sessions (twice weekly for 4 weeks) delivered during their inpatient stay.

